#### Primary Outcomes: Engagement

The primary outcome related to user engagement is defined as the overall number of modules completed within the ParentText chatbot.

#### Secondary Outcomes

##### Engagement Outcomes

Secondary engagement outcomes will include the percentage of modules and goals completed. We will also examine the rate of self-reported completion of home practice activities based on the self-reported intention to do home practice activities. In total, 3 home practice activities will involve actual interaction with the chatbot, which will allow for testing whether users lie about completing home activities when prompted. Additional engagement outcomes will include the number of days users interact with the chatbot, number of triggered safeguarding messages, number of active and passive dropout from the chatbot, number of times users use the menu and option functions, number of times users access learning through play activities and type of activity (ie, calm, active, quick, or group), type of media selected for engagement (ie, text, audio, or video), and goal selected by users after completion of the first goal. For participants in all clusters, we will compute sum scores for each engagement outcome measure for the complete study period. High engagement rates will be defined as values standing at the highest quartile of the averaged engagement score, medium engagement rates will be defined as values at the second or third quartile, and low engagement rates will be defined as values at the lowest quartile.

##### Adult and Child Behavior Outcomes

Data collection of parent- and adolescent-reported mental health and behavior outcomes will occur at 2 time points: baseline and postintervention. Outcome measurements will be standardized to capture the occurrence of practices and behaviors over the “past month (last 30 days).”

*Child maltreatment (adult and adolescent report) * will be assessed using a subset of items from the physical abuse (2 items) and emotional abuse (2 items) subscales of the International Society for the Prevention of Child Abuse and Neglect Child Abuse Screening Tool–Trial Version [73].*Positive parenting (adult and adolescent report)* will be assessed using a subset of items from the positive involvement (3 items), positive parenting (3 items), and parental supervision (3 items) subscales of the Alabama Parenting Questionnaire [74].*Parent support of education (adult and adolescent report)* will be measured using 4 items assessing how often the parent engages the adolescent in behaviors that support learning [75].*Mental health distress (adult and adolescent report)* will be measured using the 4-item Patient Health Questionnaire, which screens for anxiety and depression symptoms [76].*Parenting stress (adult report only)* will be measured using the parental stressors subscale (6 items) of the Parental Stress Scale [77].*Economic strengthening (adult report only)* will be measured using 1 item from the Financial Self-Efficacy Scale [78].*Parent-child communication (adult report only)* will be measured using items adapted from the Parent-Child Communication Scale used in the Fast Track intervention study [79].*Learning through play (adult report only)* will be assessed using a subset of items from the Alabama Parenting Questionnaire, the Parent-Child Communication Scale, and the items on parent support of education [74,75,80]. The selected scales will overarch the learning through play characteristics evidenced in the literature [57,81]. Parents will report the frequency of parent-child engagement [78].*Intimate partner relationships (adult report only)* will be investigated by assessing gender-equitable behavior. Gender-equitable behavior will be measured using items adapted from the core questionnaire in the World Health Organization multicountry study on domestic violence [82] and from questionnaires used in previous violence prevention studies [83,84].*Risk avoidance (adolescent report only)* will be assessed using 4 locally derived items on risk.*Adolescent involvement in decision-making (adolescent report only)* will be assessed to investigate to what extent adolescents’ voices are heard within families regarding decisions affecting their lives. A total of 3 items adapted from questionnaires used in previous research on parent-child engagement in decision-making will be used to assess adolescent involvement in decisions related to their education, daily activities, and money expenditure in the household [85].*Attitude toward punishment (adult and adolescent report)* will be assessed using a single item from the UNICEF Multiple Indicator Cluster Surveys 5 child discipline module [86].

ParentText also includes 1-item questions on parenting stress, parent-teenager interaction and communication, parental monitoring, teenage behavior, and intimate partner relationships that are embedded within the chatbot. These will be assessed both before and 1 week after the completion of each ParentText goal (total: 9 items).

##### Cultural Determinants of Engagement Outcomes

This study will investigate the cultural determinants associated with user engagement with ParentText through a parent-reported survey administered immediately after the in-person onboarding session. We will use the technology acceptance model 1 scale (16 items) to assess the following constructs: perceptions (ie, knowledge, attitudes, values, and beliefs affecting parents’ motivation for engaging with ParentText), enablers (ie, structural factors within society motivating parents’ engagement with ParentText, such as access to the internet), and nurturers (ie, the extent to which parents’ beliefs and attitudes are influenced and nurtured by their family, friends, and peers) [87]. Hedonic motivation (the perceived enjoyment of using the technology), habit (the extent to which an individual believes the use of a technology to be automatic), price value, and social influence were also included as additional variables to the technology acceptance model 1 due to their potential influence on the relationship between intention to use and engagement [88,89].

### Moderators and Covariates

Sociodemographic characteristics (adult and adolescent report) such as age, gender, literacy, disability, and family structure will be assessed at baseline to describe the sample population and investigate whether the intervention and components have differential effects across these subgroups.

Study assessments are summarized in Table 3.

**Table 3 table3:** Summary of study measures.

			Measurement instrument		Study period						
					Baseline		Onboarding		Intervention		Posttest
**Primary engagement outcome**											
	Number of modules completed	—^a^						✓			
**Secondary engagement outcomes**									✓		
	Percentage of goals and modules completed	—						✓			
	Rate of self–home practice activity completion	—						✓			
	Total number of interactions	—						✓			
	Number of days of interaction	—						✓			
**Behavior outcomes**											
	Child maltreatment	ISPCAN^b^ Child Abuse Screening Tool–Trial Version (4 items)		✓						✓	
	Positive parenting	Alabama Parenting Questionnaire (9 items)		✓						✓	
	Parent support of education	4 items		✓						✓	
	Mental health distress	Patient Health Questionnaire (4 items)		✓						✓	
	Parenting stress	Parental Stress Scale (6 items)		✓						✓	
	Economic strengthening	Financial Self-Efficacy Scale (1 item)		✓						✓	
	Parent-child communication	Parent-Child Communication Scale (5 items)		✓						✓	
	Intimate partner relationships	WHO^c^ multi-country study on domestic violence (4 items)		✓						✓	
	Risk avoidance	6 items		✓						✓	
	Adolescent involvement in decision-making	3 items		✓						✓	
	Attitude toward punishment	Multiple Indicator Cluster Surveys (1 item)		✓						✓	
**Moderators and covariates**											
	Cultural determinants of engagement	Technology acceptance model 1 (16 items)				✓					
	Sociodemographic characteristics and family structure	For example, age, gender, literacy, and disability		✓							
**Cost outcomes**											
	Intervention costs	Staff time and expenditures related to the preparation and delivery of specific intervention components				✓		✓		✓	
Qualitative interviews and focus groups			—								✓

^a^The outcome indicated was not collected at the referred time point.

^b^ISPCAN: International Society for the Prevention of Child Abuse and Neglect.

^c^WHO: World Health Organization.

### Qualitative Assessment

Qualitative interviews with parents will investigate their overall experiences with the chatbot-led intervention, including the enrollment and interaction process. Questions will probe participants’ perceptions regarding the acceptability, usefulness, and cultural relevance of the chatbot, WhatsApp groups, and in-person sessions. Interviews will also explore the perceived impact of the intervention on parenting and family relationships.

### Participant Timeline

The participant timeline is summarized in Figure 2. Sampling will be purposive and integrated into m2m CHAMP’s current recruitment strategy for the DREAMS project component. Recruitment will proceed until 60 parent-adolescent dyads per cluster are enrolled. Adult and adolescent participants will then be invited to an in-person session that will include (1) informed consent, (2) baseline assessment, (3) onboarding session, and (4) intention to use and cultural determinant survey (August 21, 2023, to September 8, 2023). Parents who complete the baseline assessment will receive a WhatsApp link to connect with ParentText and receive guidance on how to interact with the chatbot. The onboarding session will also include end-to-end testing to ensure that the chatbot functions correctly. Participants will be invited to interact with the chatbot for 5 minutes simulating a real-world interaction. They will then be asked to complete a paper-based assessment to collect their behavioral intention to use ParentText and cultural determinants. Depending on their assignment condition, parents will also be invited to join a facilitated WhatsApp support group or attend additional in-person sessions with their adolescent girls. The ParentText messages will be sent daily to parents via WhatsApp regardless of assignment condition. Data collectors will conduct posttest assessments approximately 6 weeks after the baseline (October 8-27, 2023). Follow-up assessments beyond the postintervention end point will not be conducted.

**Figure 2 figure2:**
[figure not shown]
Study flow diagram.

### Sample Size

The study has a fixed sample size by design with 32 clusters of equal size and equal treatment allocation across intervention arms. Sensitivity power analysis was conducted to estimate the minimum detectable effect size of the selected components on engagement and on behavior outcomes. Assuming a 2-sided test at the 10% level of significance varying the power (0.9 and 0.8) and the intracluster coefficient (0.02, 0.05, and 0.10), the minimum detectable effect ranges between a mean difference of 0.168 and 0.298 (80% power) and between a mean difference of 0.197 and 0.351 (90% power).

### Recruitment

Recruitment of participants will be based on purposive sampling relying entirely on 32 m2m CHAMP implementers and previous enrollment in the CHAMP program. CHAMP implementers will screen parents and their children to verify their eligibility for the trial. If required, recruitment will include peer-to-peer referrals in the community through respondent-driven sampling. Recruitment will proceed until 60 parent-adolescent dyads per cluster are enrolled. Participants will then be invited for a baseline assessment with trained data collectors where they will provide full written consent and complete the baseline assessment.

### Assignment of Interventions: Allocation

#### Sequence Generation

This study will adopt a cluster randomization procedure with allocation stratified by district using a parallel design. Cluster randomization will be stratified by facilitators and occur before the baseline assessments (12 clusters from Nkangala and 20 from Ehlanzeni). Random allocation will be conducted by the off-site research team in the United Kingdom using the Excel (Microsoft Corp) function “=Rand().” The in-country research team will assign clusters to 1 of the 4 experimental conditions (32 total clusters, 120 participants per cluster; 60 parents and 60 adolescent girls; N=3840 total participants). Using a 2 × 2 factorial design, this trial will randomly assign clusters so that parents receive the following engagement packages:

Engagement package 1: ParentText plus onboarding session for parents and adolescents led by an m2m facilitatorEngagement package 2: ParentText plus onboarding session for parents and adolescents and 6 moderated WhatsApp group sessions for parents only led by an m2m facilitatorEngagement package 3: ParentText plus onboarding session plus 3 in-person sessions for parents and adolescents and 6 moderated WhatsApp group sessions for parents only led by an m2m facilitatorEngagement package 4: ParentText plus onboarding session and 3 in-person sessions for parents and adolescents led by an m2m facilitator

#### Concealment Mechanism

Participants within a specific cluster and treatment condition will not be aware of the allocation of other clusters due to the geographical distance between clusters and lack of communication across groups.

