### Eligibility Criteria

Participants recruited for this trial will be parents, adolescent girls, and implementing facilitators.

Eligible clusters are communities with at least 60 households with a resident adolescent girl aged between 10 and 17 years and assigned to an m2m CHAMP implementer. Each implementer will be responsible for 60 households.

Eligible parents are those (1) aged ≥18 years and who are English, isiZulu, or siSwati speakers; (2) currently caring for an adolescent girl aged between 10 and 17 years; (3) living in the same household with the adolescent girl for a minimum of 4 nights a month over the previous 3 months; (4) having access to a mobile phone compatible with WhatsApp; (5) willing to enroll in the ParentText chatbot and receive messages via WhatsApp; and (6) who provide written informed consent to participate in the full study.

Eligible adolescents are (1) female teenagers aged between 10 and 17 years who (2) have a parent enrolled in the trial and (3) have provided written informed assent to enroll in the full study.

Eligible facilitators are (1) m2m CHAMP implementers in Mpumalanga aged ≥18 years who (2) have completed a workshop training for program delivery before the trial; (3) have a mobile phone compatible with WhatsApp and access to the internet or a data bundle; (4) speak English, isiZulu, or siSwati; and (5) have provided written informed consent to participate in the trial.

Parents with a severe learning disability or those exhibiting acute mental health disorders will be excluded due to their limited capacity to provide informed consent. Parents whose child refuses to participate in the study will not be excluded to prevent threats to internal validity. Children who have healthier relationships with their parents could be more interested in participating in the study; thus, this could lead to selection bias.

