### Assignment of Interventions: Blinding

#### Who Will Be Blinded

Due to the nature of the intervention, CHAMP facilitators, research assistants, and participants will be aware of condition allocation (based on cluster assignment). The range of conditions and allocation status of other enrolled clusters will be concealed from participants to reduce the risk of contamination. Trial statisticians conducting analyses on postintervention effects will be blinded to the assignment condition of clusters.

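### Consent follows cluster allocation, nothing withholds the arm from the implementers who enrol families, and the concealment section covers only contamination, so enrolment can depend on arm

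*Protocol article*

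**What the plan says.** All references are to the protocol article.

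- **Timing.** Sequence Generation: "Cluster randomization will be stratified by facilitators and occur before the baseline assessments".
- **Who recruits.** Recruitment describes "purposive sampling relying entirely on 32 m2m CHAMP implementers and previous enrollment in the CHAMP program", and adds that "CHAMP implementers will screen parents and their children to verify their eligibility for the trial". Peer referral is allowed if needed.
- **Who facilitates.** Eligibility Criteria defines facilitators as "m2m CHAMP implementers in Mpumalanga aged ≥18 years who" meet further conditions, among them training completed before the trial.
- **Who takes consent.** Informed Consent gives this task to the trained m2m facilitators, before baseline. Participant Timeline puts consent, baseline and onboarding into one in-person session.
- **Who knows the arm.** Who Will Be Blinded: "CHAMP facilitators, research assistants, and participants will be aware of condition allocation". The same section gives contamination as the reason for hiding other clusters' status from participants.
- **Concealment.** The one sentence under Concealment Mechanism says that participants "will not be aware of the allocation of other clusters due to the geographical distance between clusters".

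**The concern.** In a cluster trial that enrols individuals after the clusters are randomised, concealment means that the people who identify and consent participants do not know the cluster's arm, and ideally that participants do not know it when they decide. Distance between clusters does nothing for this.

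The arms ask very different things of families and staff: one in-person session of about two hours or four, and six one-hour WhatsApp groups or none. An implementer who knows the arm could favour families who are available and active on their phones, and families told of a heavier schedule could decline. Availability and phone use plausibly predict the primary outcome, the number of modules completed. Any such selection would be mixed with the component effect, and the component effects decide which package goes forward to the next trial.

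The planned analysis cannot undo this. Intention to treat preserves the groups as enrolled, including any difference created at enrolment. Table 3 records the primary outcome only during the intervention, so it has no baseline value to adjust for. Covariates remove only what was measured.

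**Working it through.** **1. Order of events.**

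| Step | What the article supports | Section |
|---|---|---|
| Randomisation | Before baseline; position relative to screening not stated | Sequence Generation |
| Screening and recruitment | By the implementers; same calendar window as baseline, August 21 to September 8, 2023 | Recruitment; Trial Status |
| Consent | By facilitators, in the baseline session | Informed Consent; Participant Timeline |
| Facilitator training | Before the trial, with four condition-specific manuals | Eligibility Criteria; Training of Facilitators |
| Disclosure of arm to implementers | Facilitators are aware; no time given | Who Will Be Blinded |

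Consent shares a session with baseline, and randomisation precedes baseline, so consent is planned after allocation. Whether the list of dyads was fixed before randomisation cannot be determined.

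**2. The plan's own figures.** Inputs: 32 clusters, hence 16 per level of each component; 60 parents per cluster; two-sided 10% level; ICC 0.02, 0.05 and 0.10 (Sample Size, Table 1). I take the stated mean differences to be in SD units.

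Design effect DE = 1 + 59 × ICC = 2.18, 3.95, 6.90.

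SE = √(2 × DE / 960) = 0.0674, 0.0907, 0.1199.

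MDE = (z for the 10% two-sided level + z for power) × SE:

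- 80% power: 0.168, 0.226, 0.298
- 90% power: 0.197, 0.266, 0.351

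The end points match the stated ranges.

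**3. What a selection shift would do.** The article gives no size for the bias, so b below is an assumption. It is the difference, in SD units, in enrolled parents' propensity to complete modules between the two levels of a component.

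Against the 80%-power MDEs, b = 0.10 gives 0.10/0.298 = 34% to 0.10/0.168 = 60%. Against the 90%-power MDEs it gives 0.10/0.351 = 28% to 0.10/0.197 = 51%.

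If the true component effect is zero, the nominal 10% test rejects with probability Φ(b/SE − 1.645) + Φ(−b/SE − 1.645):

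| b (assumed) | ICC 0.02 | ICC 0.05 | ICC 0.10 |
|---|---|---|---|
| 0.05 | 19% | 15% | 13% |
| 0.10 | 44% | 30% | 22% |

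These use the planned 60 parents per cluster.

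**4. Room for differential uptake.** The abstract reports 1009 enrolled, with a mean age of 43. If all are caregivers (an assumption), the comparable target is 1920 parents: 1009/1920 = 53%, or 1009/32 = 31.5 per cluster instead of 60. The abstract gives no breakdown by arm.

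**The case against.** **Timing.** The text says before baseline, not before recruitment. Participant Timeline and Recruitment both have 60 dyads enrolled per cluster and then invited to baseline, so lists could have been drawn up before randomisation. This stands: a reader might infer that clusters were allocated before any family was approached, and the article does not say so. It does not remove the problem, because consent still comes after allocation.

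**Knowledge at screening.** The blinding section attributes awareness to the nature of the intervention, which concerns delivery. That implementers knew the arm while screening is an inference. It is a reasonable one, given training before the trial, condition-specific manuals and the shared date window, but it is not stated. What is certain is that no section keeps the arm from them.

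**Limited discretion.** Each implementer is responsible for 60 households, the target is 60 dyads, and recruitment relies on previous CHAMP enrolment. The Implementation section also says that households are selected at random. The caseload does narrow the choice of whom to approach. Random selection contradicts the purposive sampling in two other sections and names no sampling frame or independent selector. Neither controls who consents.

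**Shortfall.** Setting 1009 against the 3840 total would probably compare caregivers with parents and girls together. Even against 1920, a shortfall does not show that uptake differed by arm.

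**Already handled.** The article plans to describe baseline differences and to adjust for age, gender and other individual covariates. That helps, and it is the right place to build, but it cannot reach unmeasured willingness to engage.

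**Conclusion.** The concern holds as a weakness of the plan as written. Formal enrolment follows allocation, the staff who enrol are the staff stated to be aware of condition, nothing withholds the arm from them, and the concealment section answers a different question. Because the article has a concealment section and fills it with contamination control, condensation of a longer protocol does not explain this.

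The article does not support the stronger readings: that allocation preceded all recruitment, that implementers chose families knowing the arm, or that enrolment actually differed by arm.

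The size is unknown. Under an assumed 0.1 SD shift the bias would be 34% to 60% of the 80%-power MDEs, and the false-positive rate would rise from 10% to between 22% and 44% over the stated ICC range. With an assumed 0.05 SD it would be 13% to 19%. Uptake of about 53% of planned parents, if all 1009 are caregivers, leaves room for differential uptake but is not evidence of it.

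**What to change.** **Design, and the text under Concealment Mechanism.** Fix each cluster's list of dyads, and complete consent and baseline, before that cluster's allocation is disclosed to its implementer and participants. Train all implementers beforehand on the common onboarding content, or on all four manuals, so that the requirement for training before the trial is still met. Disclose the arm before the arm-specific invitations, which Participant Timeline places in its account of the onboarding visit. Rewrite Concealment Mechanism to say who is kept unaware and until when, and move the sentence on distance between clusters to the discussion of contamination. Reconcile purposive sampling (Recruitment, Participant Timeline) with random selection of households (Implementation).

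**Now that recruitment has ended.**
- State when each implementer learned the arm, and whether the dyad list was already fixed.
- Report numbers approached, eligible, consented and onboarded, with baseline characteristics, by arm.
- Include measured baseline predictors of engagement among the individual-level covariates already planned.
- State the residual selection risk as a limitation of the component effects, and carry it into the choice of package.

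**Cost.** For the design: small logistics around training and disclosure, and consent wording that describes the intervention without revealing the cluster's arm. For the completed trial: reporting effort, to the extent that approach and eligibility numbers were logged. Sample size and MDE do not change.
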